### 5.5.2 SCREENING AND ENROLLMENT PROCEDURES

[figure not shown]

---

### 5.5.3 CAREGIVER PARTICIPANT RETENTION

Caregivers and teachers are asked to complete weekly RAMP Reports of the child's ADHD symptoms for 4 weeks followed by monthly RAMP Reports for 2 months. Potential concerns include the length of the RAMP Report and frequency of requests. A text-message-based platform with a direct link to radio-button style responses will be used to decrease this burden. Log-in is not required, and the instrument is formatted to be compatible with smart phone-based usage for completion. Caregiver participants will receive automated reminder prompts at 24 and 48 hours if the RAMP Report has not been completed. Study coordinators will check-in with caregiver participants to ask about any technical difficulties with the RAMP platform or barriers to completing the forms at approximately 1 week, 4 weeks, and 2 months from the time of consent.

Caregivers will be compensated for their time, engagement, and participation in the study. Caregivers will be compensated through ClinCards (or site's preferred method) after completing the enrollment visit (\$100), and after completing the 90-day [study assessment](#) (\$100). Maximum caregiver compensation is \$200. ClinCard is similar to a Visa or MasterCard debit card and is used to compensate or reimburse research participants. ClinCard is the preferred method of paying human subjects participating in industry and non-industry clinical trials with recurring visits. ClinCards are provided directly to research participants by the study teams, and the study teams utilize the web-based system to electronically issue payments onto the card. The research

coordinators will dispense ClinCards to participants, track and monitor payments issued, and ensure compliance for the study.

If the 90-day study assessment is not received within 10 days of send-out, then a phone call will be made by the research coordinator with an offer of an additional study assessment provided by the participant's preferred method. This follow-up may be repeated one additional time after an additional 10 days. These study assessments will serve as a marker of retention.

---

#### 5.5.4 PROVIDER PARTICIPANT RETENTION

Through the study period, the providers will be asked to review the data submitted by caregivers and teachers in the RAMP. An alert will be sent to the provider when new reports have been entered by a caregiver or teacher. The research coordinators will have access to the RAMP provider dashboard in REDCap and will monitor the completion of these review surveys. Each practice site will receive compensation of \$4000 for their time and engagement working on the study. Provider participants will receive an automated reminder prompt at 24 hours if the RAMP report review has not been completed. Study coordinators will check-in with provider participants to ask about any technical difficulties with the RAMP platform or barriers to completing the forms at approximately 1 week, 4 weeks, and 2 months from the time of consent. Providers will be compensated for their time, engagement, and participation in the study. Providers will be compensated through ClinCards (or site's preferred method) after signing the provider consent form (\$100), and after submitting their last provider survey (attached to the final RAMP report returned for the last child participant assigned to the provider, \$100). Maximum provider compensation is \$200. Referring potential participants to the study team is a normal activity for providers in clinical trials, and providers who join the study will not receive extra payments for referrals. Providers will not join consent encounters for their patients. Given that providers typically enjoy salaries well above the United States median income, the compensation provided should not unduly influence their decision to participate.

## 6 STUDY INTERVENTION

### 6.1 STUDY INTERVENTION(S) ADMINISTRATION

#### 6.1.1 STUDY INTERVENTION DESCRIPTION

**Research Coordinator Procedures:** A research coordinator will be identified at each of the participating ISPCTN sites to organize study procedures at the practices in their state. In the first phase, they will work with site champions at the practices to assist with scheduling the ADHD Best Practice education, RAMP platform orientations, and informed consent encounters for all providers who care for children with ADHD. In the second phase, they will describe the study to interested caregivers and complete enrollment and randomization procedures as well as complete periodic chart reviews and participate in study-related calls. Prior to the start of the first phase, they will receive training in obtaining informed consent if not experienced, given scripted language to use with families when describing the study and supporting caregivers and providers who have not completed or reviewed reports, respectively.

**Provider Training:** All providers who care for children with ADHD within the study practices will be offered ADHD Best Practice education and RAMP orientation as an introduction to the study. Providers will provide informed consent prior to the start of caregiver/child recruitment and enrollment. This will ensure that there is current knowledge of best practices for ADHD diagnosis and care available to all children receiving care for ADHD within this study. The project is not focused on provider training, as these are not new guidelines, but rather addresses other potential barriers that are unique to rural settings. In addition to this clinical training module, all providers will be required to complete training in the provider use of the RAMP platform.

**The RAMP Platform:** The technology platform used for this study will be an adaptation of an existing program used for behavioral health screening for pregnant women. This program has screened close to 400 women and has shown superior clinical outcomes compared to usual care. The RAMP will be housed in REDCap, a HIPAA-compliant data collection tool. The intervention cohort will be notified of their randomization assignment with a text message or email. They will receive text message requests to fill out the RAMP Reports below. Their responses will be compiled into a RAMP Report which will be available to the provider on their dashboard of enrolled participants.

**RAMP Reports completed by caregivers:** The RAMP caregiver interface includes monitoring of ADHD symptoms, engagement in behavioral health care visits, and progress in educational settings. These domains of information have been selected as they are typically combined by providers when making decisions regarding medication dose adjustment. The requests for reports will be sent to caregivers as a link in a text message. Upon clicking the link, they will be able to select radio button responses to questions directly on their mobile device (without any login requirement). The RAMP Report requests will be sent weekly for 4 weeks then every month for the remaining 2 months. RAMP Reports will be submittable for 72 hours after initial release. Once a new RAMP Report is available, caregivers cannot go back and complete reports for prior periods.

**RAMP Reports completed by teachers:** Caregivers in the intervention group will provide teachers with a secure, unique link to access the RAMP Platform. This link will be in the form of a QR code which can be printed on paper or emailed directly to the teacher from the caregiver. Teachers will enter the symptom information directly into the platform. The teacher's RAMP Reports are identical to caregiver RAMP Reports, will consist of the first 18 inattention/hyperactivity questions on the Vanderbilt Assessment, and will be requested at the same interval as the caregivers. We will use an approach similar to that used by Power *et al.* The responses to the teacher RAMP Reports will be available to the providers on the RAMP portal. If a child's teacher does not want to use the RAMP platform, the child will not be disqualified. If a child has multiple teachers, the caregiver should choose one teacher to participate, preferably the one that spends the most time with the child.

[figure not shown]

**Provider Report Review:** Providers will be alerted by their preferred means (text or email) when new caregiver or teacher reports are available for review. While providers will have access to the platform at all times, there will be one provider survey to document review for any given week that there is either a caregiver survey, teacher survey or both to review. .

| Record ID | DDP New Items from RDW    | Basic Demography Form | initial Vanderbilt | clinician review | 1 week RAMP | clinician review | 2 week RAMP | clinician review | 3 week RAMP | clinician review |
|-----------|---------------------------|-----------------------|--------------------|------------------|-------------|------------------|-------------|------------------|-------------|------------------|
| 11 Test1  | 1 view    |                       |                    |                  |             |                  |             |                  |             |                  |
| 12 Test2  | None view |                       |                    |                  |             |                  |             |                  |             |                  |
| 13 Test3  | None view |                       |                    |                  |             |                  |             |                  |             |                  |
| 14 Test4  | None view |                       |                    |                  |             |                  |             |                  |             |                  |

**RAMP Platform Prototype. A prototype of the dashboard that providers and research coordinators will use to review participant-entered data and monitor study activities, respectively**

The reports submitted by caregivers will be found on a different tab than those submitted by a teacher (but linked with the same ID) to clearly identify source. Providers and research coordinators will review RAMP Reports from a dashboard similar

to the figure on the right. A red dot will indicate an unreviewed RAMP Report has been entered by the participant. The provider will select the red dot to open the report from the caregiver or teacher. Following review, the provider will answer a quick 2-question, radio-button style survey regarding their response to the report. Research coordinators will be able to monitor data entry, and review and document clinical changes as a result of the report.

**Digital Education Handouts:** Digital education handouts will be sent to all caregivers in the control group on a weekly basis for 4 weeks, then monthly for 2 months. These will be sent through email, and will cover a range of general pediatric topics, such as nutrition, exercise, and screen time.

## 6.2 MEASURES TO MINIMIZE BIAS: RANDOMIZATION AND BLINDING

Following enrollment, caregiver/child dyads will be randomized into one of two treatment arms:

1. Intervention Arm: will participate in the RAMP for a period of 3 months
2. Control Arm: standard of care determined by the treating healthcare provider; digital education handouts (attention controls) distributed by the study team at the same intervals as the RAMP Report requests in the intervention group

Caregiver/child dyads who complete screening and enrollment procedures will be randomized using a stratified randomization scheme together with a varying permuted block randomization. Enrolled caregiver/child dyads from the practices will be randomly assigned to RAMP (intervention) or standard of care (control) at a 1:1 allocation ratio. Randomization will be stratified by practice (i.e., randomized within practices) to control for potential differences in study population or differences in management. Secure, practice-specific randomization lists will be generated for each site to use when randomizing a participant. At enrollment, the research coordinator will assign randomization assignments in sequential order, pulled directly from the list. Due to the nature of the intervention, it is not possible for blinding of treatment assignments to be performed in this study. All providers will receive Best Practice Education based on the 2019 AAP clinical practice guidelines, including the recommended frequency of for symptom gathering that is the basis for the planned schedule of RAMP Report requests. Therefore, providers caring for children assigned to the control group may attempt to meet this schedule. However, they will still face hardships inherent to paper forms.

Research coordinators will also make note if any paper symptom assessments are returned for the intervention arm in addition to the RAMP reports. A [study-specific assessment](#) will be done, at 90 days and will serve as a marker of retention.

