The entire timeline will span 17 months with three phases. In the first phase of the study, the providers from the participating practices will receive ADHD Best Practices education and training in the portal use, and will be asked to provide informed consent. A member of the clinic staff (nurse, medical assistant or practice manager) will be identified as site champion. The site champion will facilitate communication between the site study team and the clinic staff. The second phase of the study will focus on child/caregiver and provider utilization. Providers will identify patients with a diagnosis of ADHD who are being started on stimulant medication to be contacted by study staff for enrollment. Research coordinators will discuss the study, perform eligibility screening and obtain consent (if deemed eligible by PI). The consented caregiver/child dyads will be randomized to intervention (requests to submit the RAMP Reports for 3 months) or control (usual care with attention control) groups. Families will be approached until 36 caregiver/child dyads are enrolled (only one child in a family may be enrolled). Each practice will have 6 weeks to enroll 9 participants. After the 6 weeks, practices with low enrollment will receive additional supports. Each week, progress to target will be evaluated to determine if any practice needs additional resources. If multiple practices do not meet enrollment goals, the study team may consider relaxing exclusion/widening inclusion criteria (ex. include patients undergoing re-titration, widen age criteria) and/or opening enrollment. Enrollment will be paused for 3 months from the last month of school to the start of the new school year (beginning of May to end of July). This will decrease the burden on practices and study staff during the time of the year with the fewest number of ADHD diagnoses. Once enrolled, caregiver/child participants will be randomized to either the intervention or control group and followed for approximately 3 months. Participants randomized to the intervention group will submit RAMP reports weekly for 4 weeks and then monthly for 2 months. Participants randomized to the control group will receive digital education handouts at the same frequency as the RAMP reports in the intervention arm. Research coordinators will periodically review the child participant's EMR and mark how many paper symptom assessments are returned while enrolled on the study for both groups. Research coordinators will also access the RAMP platform to log RAMP reports returned by caregivers/teachers, RAMP reports reviewed by providers, and provider survey results. All caregiver participants will complete a 90-day Vanderbilt Assessment as a retention measure (see section 1.2.1 for more details). This phase will continue until all 36 participants have completed their 3-month study period. In the third phase, the above endpoints will be calculated, the full-scale trial will be designed, and the findings presented in a manuscript.

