### 5.5 STRATEGIES FOR RECRUITMENT AND RETENTION

#### 5.5.1 RECRUITMENT OF POTENTIAL PARTICIPANTS

Research coordinators will work with practice providers to schedule the ADHD Best Practice education, RAMP platform orientation, and informed consent encounters for providers who care for children with ADHD at each practice. ADHD Best Practice education and RAMP platform orientation will introduce providers to the study in a group setting. Providers will have an opportunity to ask questions and sign the consent documents at that time or schedule private consent encounter with a research coordinator.

Providers will notify research coordinators of potential participants following an initial evaluation visit for ADHD. Research coordinators may also search for potential participants in the EMR. A partial HIPAA waiver will be obtained for pre-screening procedures used to identify potential participants. Upon return visit and completion of ADHD diagnosis and initiation of stimulant therapy, caregiver/child dyads will receive a flyer from the provider and, if amenable, be referred to a research coordinator for remote review of the project to assess their interest. Research staff will contact interested caregivers by phone, email and/or text. If caregivers are unreachable by any of these methods at first contact, research staff will follow up with at least two additional outreach attempts by one or more methods (phone, email, and/or text) during the first five weeks after stimulant medication is initiated. After a detailed discussion of the project, if a caregiver does not want to participate, the research coordinator will ask reason for refusal and document this information (no PHI required). For all interested caregivers, the study team member will complete the eligibility screening and alert PI to review the eligibility (if needed). Enrollment procedures will include informed consent, HIPAA and FERPA authorizations, orientation to the platform and enrollment text, and obtaining demographics and baseline medical history. Research coordinators will also ask for the caregiver's permission to obtain the initial diagnostic assessment from the diagnosing clinician. Eligible caregiver/child dyads will be randomized to either intervention or control group (1:1).

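### Section 6.2 has the recruiting coordinator take assignments straight from a practice list generated for the site, which does not ensure allocation concealment

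*Protocol*

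**What the plan says.** Section 6.2 of the protocol sets out a "stratified randomization scheme together with a varying permuted block randomization", "at a 1:1 allocation ratio", with practice as the stratum. It then fixes how an arm is assigned: "Secure, practice-specific randomization lists will be generated for each site to use when randomizing a participant". The next sentence reads: "At enrollment, the research coordinator will assign randomization assignments in sequential order, pulled directly from the list". The same section says that blinding is not possible.

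The person doing this is also the recruiter. Under section 4.1 the research coordinators discuss the study with families, screen them and obtain consent. Section 6.1.1 says that in the second phase "they will describe the study to interested caregivers and complete enrollment and randomization procedures as well as complete periodic chart reviews". It also says: "A research coordinator will be identified at each of the participating ISPCTN sites to organize study procedures at the practices in their state". With two ISPCTN sites, that is one named coordinator per site.

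Section 4.1 makes consent conditional on the PI finding the dyad eligible. Section 5.5.1 asks for that PI review only where it is needed.

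**The concern.** Concealment means that whoever decides whether and when a family enters the trial cannot know the arm that comes next. A list generated for the site and used in order by the recruiter does not provide that. The word secure restricts outsiders, not the authorized user. Varying the block sizes hinders guessing, but it does not stop anyone from reading.

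The coordinator has room to act on foreknowledge. Under section 5.5.1 coordinators may search the EMR for candidates, choose how to make contact, go beyond the required minimum of two further attempts, and work within a five-week window. The trait at risk is how responsive a caregiver is. It shows during recruitment contacts and plausibly drives the primary endpoint, the number of assessments returned.

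The comparison matters even in a pilot. Section 9.1 states a hypothesis of significantly more assessments under RAMP. Section 9.4.2 plans a Poisson model and a difference with a 95% confidence interval. The results are to inform a full-scale trial. Section 4.2 accepts contamination of the control arm because it leads to false negatives rather than false positives. Steering less responsive families away from RAMP slots would push the other way. Selection of this kind cannot be reliably removed in the analysis.

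**Working it through.** The protocol gives no figure to reproduce on this point. The check is a comparison of its sections, followed by two illustrations.

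**1. Text comparison.**
- Who assigns: the research coordinator (6.2).
- From what: practice-specific lists generated for the site, taken in order (6.2).
- Who contacts, screens, consents and enrolls: the research coordinator (4.1, 5.5.1, 6.1.1).
- When: after enrollment (6.2). This protects only if the next entry could not be seen beforehand.
- Sealed envelopes, central or electronic release, an assigner independent of recruitment, or block sizes withheld from sites: not required anywhere in the available text.

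**2. How much of the sequence could be known.** Inputs: 36 dyads / 4 practices = 9 per stratum, which matches the target in section 4.1; 1:1 allocation; varying blocks. The protocol gives no block sizes, so they are assumed here. If the list can be read, 9 of 9 assignments are known. If it is hidden but past assignments are known, the best simple guess is the arm that is behind so far, with a coin toss when the arms are level. Results from 200,000 simulated strata of 9:

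| Assumed blocks | Correct guesses | Of 9 |
|---|---|---|
| 2 and 4 | 69.6% | 6.3 |
| 2, 4 and 6 | 67.5% | 6.1 |
| 4 and 6 | 66.3% | 6.0 |
| fixed 4 | 68.6% | 6.2 |

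Hand check for fixed blocks of 4: expected correct guesses per block are 1/2 + 2/3 + 2/3 + 1 = 2.833. Nine assignments are two blocks plus one more, so (2 × 2.833 + 0.5)/9 = 68.5%, in agreement. Simple randomization would give 50%, or 4.5 of 9.

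**3. What steering could do, on assumed inputs only.** Suppose that 40% of families return a mean of 2 reports and 60% a mean of 8, that RAMP has no effect, and that a share f of the low returners is diverted when the next slot is RAMP. The low share in RAMP becomes p = 0.4(1 − f)/[0.4(1 − f) + 0.6], and the RAMP mean is 8(1 − p) + 2p.
- f = 0: p = 0.400, mean 5.60
- f = 0.10: p = 0.375, mean 5.75 (+2.7%)
- f = 0.25: p = 0.333, mean 6.00 (+7.1%)
- f = 0.50: p = 0.250, mean 6.50 (+16.1%)

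For scale, take Poisson counts within each class. The variance is 5.6 + 0.4 × 0.6 × 6² = 14.24, so the SD is 3.77. The 95% half-width for a difference with 18 per arm is 1.96 × 3.77 × √(2/18) = 2.5 reports.

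**The case against.** The strongest reply is that section 6.2 never says the coordinator can see later rows. A secured list that gives up one entry at a time would also fit its words. A reader might infer that allocation is certainly unconcealed and fully predictable, but the text does not go that far. It supports the narrower statement that concealment is not ensured, with an open list as the natural reading.

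The protocol also limits steering and leaves a trail. Randomization follows enrollment, and refusal and screen-failure reasons are recorded. Coordinators use scripts and are observed from time to time. A minimum number of contact attempts is set, and enrollment must fall within 35 days of the prescription. These measures narrow the opportunity and make some abuse detectable. None of them hides the next entry from the person using the list.

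Further detail may exist elsewhere. Section 5.5.2 is a figure that was not readable in the copy used here, and other procedures are deferred to a manual of procedures that is not at hand. Neither can be assumed to cure the problem, and section 6.2 does not refer the assignment step to either.

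It is tempting to add that coordinators also abstract the outcome. That is a separate question of ascertainment. It applies only to paper forms, because RAMP Reports are time-stamped by the platform.

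**Conclusion.** The concern stands in this form: section 6.2 fixes an assignment procedure that does not ensure concealment from the person who recruits. It is a conduct rule stated in the protocol, not a detail left to the SAP.

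The size of any resulting bias cannot be computed from the document. A reader might take the 3% to 16% shifts as an estimate, or infer that one or two steered families per practice would decide the result. The document supports neither. The class split, the means and the steering rates are all assumed, and the illustrated shifts of 0.15 to 0.90 reports lie well inside a half-width of about 2.5. They would still be a systematic error carried into planning of the full trial.

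What concealment buys is the step from certain knowledge to partial guessing: from 9 of 9 to roughly 6 of 9 assignments per practice, given the assumed block sizes and a guesser who knows all past assignments.

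**What to change.** Replace the sentence on sequential assignment in section 6.2 with a concealed procedure:
- A practice-stratified, variable-block sequence is generated and held by coordinating-center (DCOC) staff who take no part in recruitment.
- It is loaded into the randomization module of the REDCap or EDC system already in use. The sequence and block sizes are hidden from all site staff.
- One time-stamped assignment is released at a time, only after consent and eligibility are locked.
- If any site list has already been released, it is withdrawn and a new sequence is generated for the remaining assignments. Reloading a sequence that site staff may have seen would conceal nothing.

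The change should be in place before further dyads are randomized. It costs a short amendment, which under the Statement of Compliance needs IRB approval before use, and modest data-management set-up. It needs no extra participants. It will not remove all guessing, because the trial stays unblinded with small strata.
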